### 2.6. Data collection and assessment of efficacy

On inclusion, demographic (age, sex, and weight) and clinical data will be collected as follows:
Diagnosis (six diagnostic groups will be established): surgery, lower airway obstruction, neurological disease, sepsis, trauma, and other diagnosis.Assessment of severity: the clinical status of the patient will be assessed by using Pediatric Index of Mortality 2 (PIM2), Pediatric Risk of Mortality III (PRISM 3), and Pediatric Logistic Organ Dysfunction (PELOD) scores prior to extubation.Size and type of endotracheal tube (cuffed or uncuffed).Route of intubation (oral or nasal).Previous need for endotracheal tube replacement.Previous airway endoscopies.Respiratory infection confirmed by endotracheal aspirate culture.Presence of blood in endotracheal aspirate.Duration of endotracheal intubation prior to extubation (in days).

The primary endpoint is the reduction of the incidence of moderate to severe UAO symptoms within 48 h after extubation. Moderate to severe UAO symptoms will be considered if stridor or a Taussig score of more than 5 is present. The secondary endpoints are the presence of reintubation and the potential secondary effects associated with dexamethasone.

A record of the following variables will be kept at 15 min and 1, 2, 6, 12, 24, and 48 h after extubation:
UAO Taussig score [13], a clinical scoring system for the assessment of UAO severity; evaluating stridor, retractions, inflow of air into the lungs, cyanosis, and consciousness (Table 1). Presence of inspiratory stridor.Need for and frequency of additional therapies for respiratory distress: adrenaline or nebulized budesonide, intravenous steroids, heliox, or non-invasive ventilation.Hemodynamic (blood pressure and heart rate) and respiratory (peripheral oxygen saturation and respiratory rate) parameters.Arterial partial pressure of carbon dioxide (pCO_2_) and partial pressure of oxygen (pO_2_) and glycemia. Blood samples will not be routinely collected; they will be drawn only for clinical purposes.Need for reintubation, time point, and cause.Presence of digestive bleeding.Occurrence of infection.

**Table 1 Tab1:** SPIRIT (Standard Protocol Items: Recommendations for Interventional Trials) Schedule of Events Timeline: enrolment, assessment of safety, assessment of efficacy, and dispensing of the medicine

Tests	Screening	First visit prior to extubation	Visits 2 to 8

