**Assessment of safety**			
Physical examination	X	X	X
Vital signs	X	X	X
Assessment of adverse events		X	X
Previous and current medications	X	X	X

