### 2.8. Statistics

Categorical variables will be expressed as frequencies and percentages. Normality of continuous data will be assessed by the Kolmogorov–Smirnov test. Continuous variables will be expressed as mean values and standard deviation or as median values and interquartile range.

To compare the primary endpoint of outcome between the group receiving dexamethasone and the group receiving placebo, Z-test statistics will be used. Per-protocol analysis will be performed. An intention-to-treat analysis will be performed to guarantee the effect of randomization.

The association between other categorical variables will be assessed by chi-squared test or Pearson’s coefficient or by Fisher’s exact test, as appropriate, based on the sample size. Continuous variables will be compared by Student’s *t* test or Mann–Whitney *U* test. In comparisons of values with respect to time, Student’s *t* test of repeated measures or Wilcoxon test will be performed, as appropriate. Additional subgroup analysis according to age and pathologies will be performed.

Bilateral statistical tests will be used at a 5% level of significance. Statistical analysis will be performed by using SPSS version 20 (SPSS Inc., Chicago, IL, USA).

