## 3. Discussion

Post-extubation UAO is a common complication that affects up to a third of patients, causing stridor and respiratory distress that require reintubation in 6–13% of patients [1–3]. There is no conclusive evidence of the effectiveness of steroids in preventing post-extubation UAO in pediatric patients [4]. If steroids were proven to be effective, they would become the standard treatment for those patients. This would help reduce morbidity and mortality, the length of hospital stay, the duration of mechanical ventilation, and hospital costs [1, 2, 5, 6].

On the basis of the limited evidence currently available, we designed a multicentric, randomized, double-blind study. The primary endpoints are post-extubation UAO symptoms, as they reflect the effects of steroids adequately. Reintubation is the most severe consequence of extubation failure and is the factor with the most significant impact on prognosis [2, 4]. Yet, as the incidence of reintubation is low, the number of patients needed for detecting differences between treatment groups would be very high. In addition, the recruitment of pediatric patients of these characteristics, who are often critically ill, is challenging. Therefore, the reduction in the incidence of reintubation, together with the occurrence of adverse events, was established as a secondary objective.

Prolonged reintubation is one of the most significant risk factors for reintubation [1, 5]. Considering the evidence provided in the literature [1, 3, 4, 11], we decided to use intubation for more than 48 h as an inclusion criterion. We included other risk factors reported to be associated with UAO [1, 2], namely tube size and characteristics (cuffed or uncuffed), underlying respiratory diseases, and previous manipulation of the airway. We decided to exclude patients who have received corticosteroids within the previous seven days given that the biological half-life of dexamethasone is 36–54 h and the elimination is completed (94%) after 4 half-lives.

Steroids are used for the management of multiple diseases. Although they involve some risks, the administration of four doses of steroids for prophylaxis of the UAO after extubation is not expected to cause significant adverse events [4, 7, 11]. Therefore, the potential benefit of steroids would outbalance its associated risks.

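### The unadjusted t or Mann-Whitney test stated for continuous variables is valid for post-extubation blood pressure, but gives up precision that age and screening blood pressure could supply

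*Protocol article*

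**What the plan says.** Section 2.8 gives the between-arm method for continuous variables as "Continuous variables will be compared by Student’s *t* test or Mann–Whitney *U* test". It adds paired tests for changes over time, which are within-patient comparisons, and subgroup analyses by age and pathology. Categorical variables have their own sentence: "The association between other categorical variables will be assessed by chi-squared test or Pearson’s coefficient or by Fisher’s exact test, as appropriate".

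Section 2.6 sets the measurement schedule: "A record of the following variables will be kept at 15 min and 1, 2, 6, 12, 24, and 48 h after extubation". The list that follows includes "Hemodynamic (blood pressure and heart rate) and respiratory (peripheral oxygen saturation and respiratory rate) parameters". Age is available at entry: "On inclusion, demographic (age, sex, and weight) and clinical data will be collected as follows". In the safety block of Table 1, the row "Vital signs X X X" schedules vital signs at screening, at the first visit before extubation and at visits 2 to 8.

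On the role of these data, section 2.6 states: "The secondary endpoints are the presence of reintubation and the potential secondary effects associated with dexamethasone". The Discussion lists hypertension among the side effects of steroids.

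**The concern.** Normal blood pressure rises through childhood. In a sample running from 1 month to 16 years (section 2.2), part of the variation between children is therefore age and has nothing to do with treatment. A further part is each child's own level before treatment. An unadjusted comparison leaves both in the error term. Allocation is by simple randomization with no stratification stated (section 2.4), so a chance age imbalance also adds noise to the difference.

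At stake is the width of the confidence interval for a blood-pressure effect of dexamethasone. If it is wider than the data allow, a modest rise is easier to miss. The Discussion expects no significant adverse events from four doses, and a needlessly wide interval supports that expectation weakly. The article gives a numerical criterion for severe hyperglycemia (section 2.7) but none for hypertension, so the continuous readings are the clearest stated route to a blood-pressure effect.

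**Working it through.** **Sample size first.** The sample size text under section 2.7 gives 110 per arm for the binary primary endpoint (h = 0.4, 80% power, two-sided 5%, 10% loss).
- n = 2 × (1.96 + 0.8416)² / 0.4² = 98.1, so 99 evaluable per arm.
- 99 / 0.90 = 110. The stated figure is reproduced, and 99 per arm is used below.

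**Inputs for blood pressure.** The document gives none, so these are all assumptions, chosen to span a range. Mean blood pressure is taken as linear in age.
- Mild case: 20 mmHg rise over the age range, ages log-uniform, within-age SD 12 mmHg. Between-age SD = 4.90.
- Strong case: 40 mmHg rise, ages uniform, within-age SD 10 mmHg. Between-age SD = 40/√12 = 11.55.
- Within-age correlation (rho) between screening and post-extubation values: 0.5, varied to 0.3 and 0.7.

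**Variance due to age.**
- Mild: raw SD = √(12² + 4.90²) = 12.96; R² = 4.90²/12.96² = 0.143; unadjusted SE exceeds age-adjusted SE by 12.96/12 − 1 = 8%.
- Strong: raw SD = √(10² + 11.55²) = 15.28; R² = 0.571; excess = 15.28/10 − 1 = 53%.

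**Detectable difference at one visit** = 2.8016 × SD × √(2/99) = 0.398 × SD. With age and baseline as covariates, SD = within-age SD × √(1 − rho²); at rho 0.5 this is 12 × 0.866 = 10.39 (mild) and 10 × 0.866 = 8.66 (strong).

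| Analysis (rho 0.5) | Mild, mmHg | Strong, mmHg |
|---|---|---|
| Unadjusted | 5.16 | 6.08 |
| Age only | 4.78 | 3.98 |
| Age and screening value | 4.14 | 3.45 |

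The fully adjusted figures at rho 0.3 and 0.7 are 4.56 and 3.41 (mild), and 3.80 and 2.84 (strong).

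**The same in SD units.** If R is the overall correlation of the outcome with the covariates, the SE falls by the factor √(1 − R²). The detectable difference of 0.40 SD becomes 0.38 (R = 0.3), 0.34 (R = 0.5) or 0.28 (R = 0.7). Power for a 0.40 SD difference rises from 80% to 84%, 90% and 98%.

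**Validity.** In simulations with no treatment effect (4000 replicates per scenario, 99 per arm or 198 in all), the unadjusted t test rejected 4.8–5.2% of the time in the blood-pressure scenarios. In standardized data the t and Mann-Whitney tests rejected 5.4–5.6%. The Monte Carlo SE is √(0.05 × 0.95/4000) = 0.34 percentage points, so these are close to nominal. The mean difference was within 0.06 mmHg of zero in the blood-pressure scenarios.

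**A t test on change from screening** would fit the wording of 2.8, although it is not stated. With equal SDs and the same age slope at both times, its SD is within-age SD × √(2(1 − rho)).

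| rho | Mild, mmHg | Strong, mmHg | SE relative to ANCOVA, √(2/(1 + rho)) |
|---|---|---|---|
| 0.3 | 5.65 | 4.71 | 1.24 |
| 0.5 | 4.78 | 3.98 | 1.15 |
| 0.7 | 3.70 | 3.08 | 1.08 |

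In the mild case at rho 0.3 it is worse than no adjustment (5.65 against 5.16). With unequal SDs the ordering can close: the two methods coincide when rho × SD(post)/SD(pre) = 1. For rho 0.8 and an SD ratio of 1.25, the change variance is 1.5625 + 1 − 2 × 0.8 × 1.25 = 0.5625, and the ANCOVA variance is 1.5625 × (1 − 0.64) = 0.5625.

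**The case against.** The strongest reply is that nothing here is an error. The test is valid, the sentence in 2.8 is a general one for all continuous variables, and covariates for one vital sign are commonly left to an analysis plan that is not shown. No passage makes mean blood pressure an endpoint. The Discussion frames the safety aim as occurrence: "together with the occurrence of adverse events, was established as a secondary objective". Hypertension counted as an event would go to the chi-squared or Fisher test. The plan does use age, in subgroup analyses. All the magnitudes are assumed, and the document names no important blood-pressure difference to judge them against.

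Much of this stands, and it limits the point to an optional gain. It does not remove it. The article names a method rather than leaving it open. An event count gives no blood-pressure difference, and the article states no criterion for hypertension. Comparisons within age bands remove some of the age spread, but they do not yield one adjusted overall estimate. Section 2.6 also promises that interventions affecting the upper airway will be taken into account in the analysis, but that concerns airway events, not age or baseline blood pressure.

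A further fair objection concerns the outcome summary. An equal-weight mean over the seven visits would be debatable. With four doses 6 h apart and the first 6–12 h before extubation, the last falls 18 − 12 = 6 h to 18 − 6 = 12 h after extubation, so the 48 h reading comes at least 36 h later and could dilute a transient rise. The point does not depend on averaging, since the gain is present at a single visit.

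**Conclusion.** The point holds as an optional efficiency gain for one part of a secondary safety endpoint. At one visit, with 99 evaluable children per arm and rho 0.5, adjustment for age and screening value lowers the detectable difference from about 5.2 to 4.1 mmHg (mild) or from 6.1 to 3.4 mmHg (strong). In the mild case age alone contributes little (5.2 to 4.8), and the rest depends on the assumed correlation with the screening value. A change-score t test would recover only part of the gain when SDs are equal at both times, and can match ANCOVA when they are not.

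A reader might infer that the unadjusted test is biased or invalid, or that the trial's main result is at risk. The documents do not support either. Randomization protects the comparison, the primary endpoint is binary and compared by a Z-test, the sample size rests on that endpoint, and the stopping rule rests on the incidence of airway obstruction and severe adverse events. Nor does 2.8 rule out adjustment; it states an unadjusted method and no other.

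**What to change.** Add to section 2.8: 'Blood pressure at the scheduled post-extubation visits is compared between arms by ANCOVA with age and screening blood pressure as covariates, or by a mixed model across visits with visit-specific treatment effects and the same covariates; the adjusted difference is reported with its 95% CI.' Choose one of the two in advance; the mixed model is the better choice if many readings are expected to be missing. A mean over the seven visits is not required.

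Use the screening value as baseline. The first visit before extubation also covers randomization and dispensing in Table 1, and the article does not say whether its vital signs precede the first dose. This assumes that the screening vital signs include blood pressure; if they do not for some children, adjustment for age alone still helps.

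The cost is one sentence. Age, screening vital signs and the seven readings are already scheduled, SPSS fits the model, and no external reference values are needed. Recruitment was still open at publication, so the wording could be fixed before final unblinding.

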Baranwal et al. [3] compared two regimens in high-risk pediatric patients: starting dexamethasone therapy 6 h versus 24 h before extubation. The authors found that the 24-h regimen, as compared with the 6-h regimen, significantly reduced the incidence of UAO.

A Cochrane’s systematic review [4] concluded that the effectiveness of steroids in preventing UAO in children has not been sufficiently demonstrated, and further studies are needed to assess its potential benefits, especially in high-risk patients.

In light of the lack of consistent evidence, we designed a randomized study to compare the effectiveness of dexamethasone versus placebo in the prevention of post-extubation UAO in high-risk pediatric patients (>48 h intubated).

The main objective of this study is to explore whether dexamethasone is effective in preventing and reducing the severity of UAO symptoms in critically ill children versus placebo. Secondary objectives include investigating whether dexamethasone reduces the incidence of reintubation and evaluating the potential secondary effects associated with this medication.

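### For values recorded over time, the protocol names only within-child, two-time-point tests and no between-arm analysis of the course over the seven visits

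*Protocol article*

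**What the plan says.** Section 2.8 of the protocol article assigns tests by type of variable.

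- Primary endpoint: "To compare the primary endpoint of outcome between the group receiving dexamethasone and the group receiving placebo, Z-test statistics will be used".
- Other categorical variables: "The association between other categorical variables will be assessed by chi-squared test", with Pearson's coefficient or Fisher's exact test as alternatives.
- Continuous variables: "Continuous variables will be compared by Student’s" t test or the Mann–Whitney U test.
- Serial values: "In comparisons of values with respect to time", a Student's t "test of repeated measures or Wilcoxon test will be performed, as appropriate".

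Section 2.6 sets the schedule: "A record of the following variables will be kept at 15 min and 1, 2, 6, 12, 24, and 48 h after extubation". The list includes the Taussig score, blood pressure, heart rate, oxygen saturation, respiratory rate, blood gases and glycemia. It adds that blood is drawn only when clinically needed. The schedule in Table 1 also has vital signs and the Taussig scale before extubation.

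The main objective in section 1 is whether dexamethasone "is effective in preventing and reducing the severity of UAO symptoms in critically ill children versus placebo". Section 2.6 adds: "The secondary endpoints are the presence of reintubation and the potential secondary effects associated with dexamethasone". The Discussion names hyperglycemia and hypertension among the side effects of steroids.

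**The concern.** Mann–Whitney is named one sentence earlier, so Wilcoxon in the rule for serial values most naturally means the paired signed-rank test. Together with the repeated-measures t test, the rule then offers only before-after comparisons within children. Neither test has an arm term, and neither handles more than two of the seven visits at once.

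Heart rate, blood pressure and breathing effort can change after extubation whatever the child received. A significant change over time therefore says nothing about the drug. Nor does a significant change in one arm beside a non-significant one in the other show that the arms differ.

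At stake are the parts of the trial's question that rest on serial data. One is how severe obstruction becomes over 48 h, beyond the yes/no primary endpoint. The other is the effect of dexamethasone on vital signs. Blood pressure matters most here: hypertension is named as a side effect, but the article gives no yes/no definition for it, unlike severe hyperglycemia in section 2.7.

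**Working it through.** **1. The plan's own figure.** No stated figure depends on this point. The sample size is checked only because it is used below. With Cohen's h = 0.4, two-sided 5% and 80% power:

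n = 2 × ((1.960 + 0.842) / 0.4)² = 98.1, rounded up to 99; 99 / (1 − 0.10) = 110 per arm.

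This agrees with the protocol. Using the exact h for 33% against 16% (0.4008) gives 98, then 109.

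**2. What each named test compares.**

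| Rule in section 2.8 | Contrast | Compares the arms? | Uses seven visits jointly? |
|---|---|---|---|
| Z-test, primary endpoint | arm vs arm | yes | not needed (one outcome per child) |
| Chi-squared / Fisher | association of categorical variables | yes, when arm is one of them | not needed for yes/no outcomes |
| Student's t / Mann–Whitney | two independent groups | yes, one visit or change score at a time | no |
| Repeated-measures t / Wilcoxon | two times within a child | no | no |

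The only rule written for values over time is the one that does not compare the arms.

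**3. What the paired tests can and cannot show.** Assumptions: 110 children per arm, two visits, SD 1, within-child correlation 0.5, two-sided 5%, 3,000 simulated trials. The documents give neither the SD nor the correlation.

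The SD of a within-child change is √(2 × (1 − 0.5)) = 1, so its standard error in one arm is 1/√110 = 0.095.

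| True change (dexamethasone / placebo) | Paired test, dexamethasone | Paired test, placebo | Paired test, arms pooled | One arm significant, the other not | Between-arm test of change |
|---|---|---|---|---|---|
| +0.3 / +0.3 SD | 88% | 87% | 99% | 21% | 5% |
| +0.19 / +0.19 SD | 50% | 52% | 81% | 50% | 6% |
| +0.2 / −0.2 SD | 56% | 54% | 4.5% | 50% | 83% |

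In the first two rows the arms do not differ. The between-arm test rejects at about its nominal 5%, while the paired tests reject often because time has an effect. In the third row the arms do differ, and the pooled paired test misses it.

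**4. Check on the discordance.** If each arm's paired test has power w and the arms do not differ, the chance that exactly one is significant is 2w(1 − w). For w = 0.2 this is 2 × 0.2 × 0.8 = 32%. For w = 0.5 it is 2 × 0.5 × 0.5 = 50%, the maximum, which matches the second row.

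**5. The fallback of testing arms visit by visit.** Seven tests per variable at an unadjusted 5% would give a chance of at least one false positive of 1 − 0.95⁷ = 30% if visits were independent. It is lower when visits are positively correlated, as they would be here. Either way there is no single estimate of the treatment effect over 48 h.

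**The case against.** The strongest reply is that section 2.8 offers two kinds of comparison, between groups and over time, each with a suitable test. The two-sample t and Mann–Whitney tests can compare dexamethasone with placebo at any visit or on change scores. A paired test is right for change within children. This stands as far as it goes: the section nowhere says that the paired tests replace the arm comparison, and they may be meant as description only. It does not say that either, and it leaves the between-arm analysis of the course undefined.

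A reader might infer that side effects and severity cannot be compared between arms at all. The documents do not support that. The primary endpoint has its own between-arm Z-test, and severity enters it through the moderate-to-severe threshold. Reintubation, digestive bleeding, infection and severe hyperglycemia are yes/no outcomes covered by the chi-squared or Fisher tests.

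A reader might also multiply variables by visits by arms to get an expected number of false positives. That count has no basis in the text. It supposes separate testing in each arm at every visit, no true change over time in any variable, and routine blood sampling, which section 2.6 rules out. Likewise, no passage plans to infer a drug effect from one significant and one non-significant paired test. The 50% figure shows what such a reading would risk, not what the protocol proposes.

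Finally, this is a condensed article, and a fuller analysis plan may settle the matter. That limits the weight of the point. It does not remove it, because the article names a method that does not fit the question rather than staying silent.

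**Conclusion.** The point holds in limited form. For serial values the protocol names only within-child, two-time-point tests, which neither compare dexamethasone with placebo nor use the seven visits together. The general two-sample rule would at best give separate, unadjusted comparisons per visit with no overall estimate.

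The sample size, the primary analysis and the yes/no secondary outcomes are untouched, so this is a cheap improvement to secondary analyses and not a threat to the main result. It rests on reading Wilcoxon as the signed-rank test. The simulated percentages depend on the assumed SD, correlation and courses. The qualitative result, that a test of time is not a test of treatment, does not.

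**What to change.** In section 2.8, or in the analysis plan before final unblinding:

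- **Blood pressure, heart rate, respiratory rate, saturation:** replace the paired tests with one between-arm analysis per measure, for example a linear mixed model with arm, visit, arm-by-visit and the pre-extubation value. Report the between-arm difference over 48 h with its 95% confidence interval.
- **Taussig score:** compare the maximum over 48 h between arms, and state how scores after a reintubation are handled.
- **Glycemia and blood gases:** treat as exploratory. They are sampled only on clinical grounds, and a mixed model does not cure selective sampling.
- **Within-arm before-after tests:** if kept, label them as descriptive and draw no conclusion about treatment from them.

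The cost is wording and slightly more modelling. SPSS can fit such models, and the measurements, including pre-extubation vital signs, are already scheduled. The mixed model brings a missing-at-random assumption for missed visits, which is open to question for children who are reintubated and should be stated.
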